## Abstract

**Background:**

Smoking during pregnancy is the most important preventable cause of adverse pregnancy outcomes, yet smoking cessation support (SCS) is inconsistently provided. The MOMHQUIT intervention was developed to address this evidence-practice gap, using the Behaviour Change Wheel method by mapping barriers to intervention strategies. MOHMQuit includes systems, leadership and clinician elements. This implementation trial will determine the effectiveness and cost-effectiveness of MOHMQuit in improving smoking cessation rates in pregnant women in public maternity care services in Australia; test the mechanisms of action of the intervention strategies; and examine implementation outcomes.

**Methods:**

A stepped-wedge cluster-randomised design will be used. Implementation of MOHMQuit will include reinforcing leadership investment in SCS as a clinical priority, strengthening maternity care clinicians’ knowledge, skills, confidence and attitudes towards the provision of SCS, and clinicians’ documentation of guideline-recommended SCS provided during antenatal care. Approximately, 4000 women who report smoking during pregnancy will be recruited across nine sites. The intervention and its implementation will be evaluated using a mixed methods approach. The primary outcome will be 7-day point prevalence abstinence at the end of pregnancy, among pregnant smokers, verified by salivary cotinine testing. Continuous data collection from electronic medical records and telephone interviews with postpartum women will occur throughout 32 months of the trial to assess changes in cessation rates reported by women, and SCS documented by clinicians and reported by women. Data collection to assess changes in clinicians’ knowledge, skills, confidence and attitudes will occur prior to and immediately after the intervention at each site, and again 6 months later. Questionnaires at 3 months following the intervention, and semi-structured interviews at 6 months with maternity service leaders will explore leaders’ perceptions of acceptability, adoption, appropriateness, feasibility, adaptations and fidelity of delivery of the MOHMQuit intervention. Structural equation modelling will examine causal linkages between the strategies, mediators and outcomes. Cost-effectiveness analyses will also be undertaken.

**Discussion:**

This study will provide evidence of the effectiveness of a multi-level implementation intervention to support policy decisions; and evidence regarding mechanisms of action of the intervention strategies (how the strategies effected outcomes) to support further theoretical developments in implementation science.

**Trial registration:**

ACTRN12622000167763, registered February 2nd 2022.

**Supplementary Information:**

The online version contains supplementary material available at 10.1186/s13012-022-01250-3.

Contributions to the literature
MOHMQuit, an evidence-based systems-change intervention, will be implemented at nine public maternity services using existing health care capacity.This trial explicitly tests a theory and framework-driven approach relative to many earlier interventions which were less clearly built on implementation science frameworks and will provide further empirical evidence of the effectiveness of this approach.A comprehensive suite of measures will examine effectiveness and cost-effectiveness; and test mechanisms of action of the intervention strategies and factors impacting implementation to advance the field of implementation science.

## Background

Smoking during pregnancy is the most important preventable cause of adverse pregnancy outcomes, maternal-foetal health complications and ongoing developmental complications in the infant [1, 2]. Smoking during pregnancy doubles or triples the risk of multiple complications including stillbirth, preterm birth and low birth weight and birth defects and sudden infant death syndrome [1, 3–5]. Smoking also increases the health risks to the mother, including her risk of developing cancer, coronary heart disease and stroke; all of these are significantly reduced if women stop smoking during pregnancy [2]. Quitting smoking at any stage of pregnancy is beneficial to both mother and baby, and quitting in the first half of pregnancy reduces the risk of preterm birth and small for gestational age babies to that of non-smokers [3]. Reducing smoking rates in pregnancy is a key priority in health systems around the world to reduce the increased morbidity and mortality in mothers and babies and optimise children’s development in the first 2000 days [6–9].

In 2019, 9.0% of pregnant women in Australia smoked in the first half of pregnancy, with most (75%) continuing to smoke in the second half [10]. Higher smoking rates are found in pregnant women who live in remote areas of Australia, are of low socio-economic status, of Aboriginal or Torres Strait Islander identity or are teenage mothers [11–13]. As such, smoking in pregnancy is considered a major public health concern and supporting women to quit smoking in pregnancy can help reduce the health inequities faced by these women and their children [6, 14]. Although many pregnant women are highly motivated to quit, they face significant challenges including lack of consistent, effective support from health professionals [15, 16], despite evidence that shows that when clinicians offer consistent smoking cessation support (SCS) using psychosocial interventions it helps pregnant women to quit [17]. Pooled data from a Cochrane systematic review also found that among women who received these interventions there was a 17% reduction of infants born with low birthweights and a 22% reduction in neonatal intensive care admissions [17].

Evidence-based Australian guidelines [14, 18] recommend routine SCS be delivered during antenatal care for all pregnant women using brief interventions based on the 5As (Ask, Advise, Assess, Assist and Arrange follow-up) and include providing nicotine replacement therapy (NRT) if women are otherwise unable to quit. However, provision of recommended SCS to pregnant women has remained persistently poor [19–21]. A state-wide survey of women’s experiences of maternity care in New South Wales (NSW) found that only 46% of women who smoked in pregnancy recalled being told about quitting programs [22]. Midwives, obstetricians and managers all reported major gaps in care, particularly in assisting women with cessation strategies and arranging follow-up [23, 24], both of which are crucial to quitting success [25, 26]. Despite the availability of guidelines and training, maternity care services have faced considerable barriers in implementing SCS [23, 27] illustrating the persistence of an evidence to practice gap. One possible reason for the gap has been lack of comprehensive and theoretically informed interventions to support services in delivering SCS, suggesting a theoretically underpinned systems change approach to guideline implementation is needed [28, 29].

Systems change interventions in public health services have been shown to be effective in increasing identification of smokers by clinicians and documentation of smoking status in electronic medical records, improving integration of SCS into usual care, and increasing the numbers of referrals to telephone Quitline services [30–32]. However, to date, only one adequately powered trial has tested the effectiveness of theoretically informed implementation strategies in antenatal settings [33].

In addition to the need to select implementation strategies based on theory with a clear specification of the interventions [34], there have been recent calls for more rigorous testing of *how* implementation strategies work (or do not)—the mechanisms of action of the implementation strategies [35, 36]. To achieve this, implementation strategies need to be based on a sound understanding of the barriers to implementation and clearly explicate how the strategies are intended to address the identified barriers, thus generating testable hypotheses to assess if the strategy worked—or how multiple strategies may work together to achieve the desired outcome [35, 36]. This approach will assist to advance the scientific basis of implementation research.

## Methods

### The implementation intervention-MOHMQuit

To better support clinicians in helping women to stop smoking in pregnancy we developed a systems-change intervention (MOHMQuit: Midwives and Obstetricians Helping Mothers to Quit), using a theoretically underpinned intervention development process, the Behaviour Change Wheel [37]. The process of developing the MOHMQuit intervention is described in depth elsewhere [15]. Briefly, we used the Theoretical Domains Framework—a framework of psychological constructs in behaviour change theory [38]—to identify barriers and enablers clinicians faced to providing evidence-based SCS during antenatal care. We undertook qualitative research with maternity service managers, midwives and obstetricians [23] and a state-wide cross-sectional anonymous survey of midwives working in antenatal care [24]. Working closely with key stakeholders in the NSW public health system we then applied the steps of the Behaviour Change Wheel method [37] to develop the initial MOHMQuit intervention. This was followed by a trial at one site to determine the feasibility and acceptability of the intervention with maternity service leaders and midwives [15]. Following further refinements, the implementation, effectiveness and cost-effectiveness of the MOHMQuit intervention is now being tested. MOHMQuit is a multi-strategy systems-change intervention designed to be sustainable, which addresses identified barriers and enablers for clinicians providing SCS and ensures ongoing support for SCS amongst service managers.

The intervention includes multiple strategies with systems, leadership and clinician elements (see Additional file 1 which maps the intervention types and behaviour change techniques to the previously identified barriers). The systems change elements include building leadership capacity, improving recording of SCS in *e*Maternity (the electronic health record used by maternity services in NSW), and various resources for both leaders and clinicians, as described below. All maternity service leaders, clinicians, and Aboriginal health workers will be asked to complete two NSW Health Education and Training Institute (HETI) [39] online modules to ensure basic knowledge of smoking cessation prior to MOHMQuit-specific training. (See Table 1 for definitions of maternity service leaders, clinicians and Aboriginal health workers used in this research.) MOHMQuit includes provision of a range of resources with a series of workshops held at each site to train and support participants in their use. All workshops use evidence-based behaviour change techniques (e.g. social comparison, modelling, behavioural practice/rehearsal, reframing smoking) [37, 40, 41]. To maximise the sustainability of the intervention, midwifery educators will be trained in providing ongoing MOHMQuit training, and sites will be supported by the development of a ‘Community of practice’ to provide additional and ongoing peer support and encouragement. Additional details of the delivery of the intervention are given below and in Additional file 2.

**Table 1 Tab1:** Maternity service leaders, clinicians, and Aboriginal health workers

Personnel	Role/s in maternity services relevant to MOHMQuit
Maternity service leaders	Defined as maternity service leaders who support or supervise clinicians providing antenatal care at each site, its catchment and associated services. These include clinical midwifery consultants, maternity unit managers, clinical midwifery educators, clinical midwifery specialists, clinic coordinators, obstetric leads and others in leadership positions (these may vary slightly by site).
Clinical midwifery educators	Clinical midwifery educators are experienced midwives who undertake additional roles to maintain and advance the clinical practices of maternity care clinicians, working within professional development frameworks to support ongoing education [42, 43]. Midwifery educators play crucial roles in the quality and safety advancement of health services, helping to ensure safe practices are maintained and required clinical competencies are achieved [42].
Maternity care clinicians	All midwives, obstetricians and obstetric trainees providing antenatal care.
Aboriginal health workers	All Aboriginal health workers who provide antenatal care. Aboriginal health workers are primary health care workers who provide clinical and primary health care, supporting women independently or with other maternity care clinicians to ensure the provision of culturally safe maternity care [44, 45].

#### Maternity service leaders’ workshop

The 3-h maternity service leaders’ workshop is designed to enhance leadership in supporting clinicians to provide SCS. The workshop will be conducted by a senior midwifery trainer. Leaders will be provided with a range of resources and supported to use them to enhance service delivery. On workshop completion, leaders will be asked to: encourage and support clinical staff to attend the relevant training (see below); complete an action planning tool and review annually; identify, develop and maintain a local smoking cessation support champion; develop local care pathways for smokers; and other actions guided by their action plan. Additionally, leaders will be asked to review *e*Maternity reports monthly and discuss with their team as part of an audit and feedback process to improve professional practice [46] and help contribute to the effective implementation of the intervention [47].

#### Clinician workshops

Training for clinicians will be jointly provided by a midwifery trainer and a smoking cessation training expert. The workshops will demonstrate use of a suite of resources, with opportunity to practise their use, with the aim of building confidence and skills in supporting smoking cessation. Training for midwives and Aboriginal health workers will be provided in a 1-day workshop, while training of approximately 2 h will be provided for obstetricians and obstetric trainees. As an incentive for participation, continuing professional development points will be awarded for all clinicians.

#### Clinical midwifery educator training

Clinical midwifery educators will be provided training and resources to continue to deliver training following the intervention phase, to address issues of staff turnover or absence, in order to maximise sustainability of the intervention. Clinical midwifery educators will attend the 1-day training with the midwives and Aboriginal health workers, and then an additional 1 h training on how to provide the training themselves.

#### Development of a community of practice

Sites will be encouraged to participate in an online ‘Community of practice’ to provide additional and ongoing peer support and encouragement. Senior members of the research team will also provide ongoing support for the implementation of MOHMQuit across all sites at these monthly meetings. Each site will be added to the Community of practice meetings after training occurs at their site.

The implementation logic model, with data collection to evaluate it, is shown in Fig. 1.

**Fig. 1 Fig1:**
[figure not shown]
MOHMQuit implementation logic model

### Study design

The study is being undertaken as a partnership between academic researchers, policy makers within NSW State Government and non-government agencies and senior clinicians from participating sites. At each site, there is a Midwifery Partner Investigator and an Obstetric Partner Investigator supporting implementation of the trial.

The MOHMQuit trial is a pragmatic stepped-wedge cluster-randomised controlled trial of an implementation intervention in nine public maternity services in NSW. Our overarching goal is to increase smoking cessation among pregnant women to improve health outcomes. This trial will test the effectiveness and cost-effectiveness of the MOHMQuit intervention in achieving this, while also testing the mechanisms of action of the strategies based on the underpinning theoretical development of MOHMQuit. The specific aims of the trial are to compare the effectiveness of MOHMQuit versus usual care in increasing:Smoking cessation among pregnant women attending public antenatal services in NSW;The provision of guideline-recommended SCS as documented in *e*Maternity;Participating clinicians’ self-reported provision of guideline-recommended SCS to pregnant women;Participating clinicians’ knowledge, skills, confidence and positive attitudes regarding providing guideline-recommended SCS to pregnant women; andWomen’s reported receipt of cessation advice, resources and referral to quit smoking services.

Additional aims include the following:6.Determining the cost-effectiveness of the intervention in increasing smoking cessation;7.Assessing implementation of the intervention through a detailed process evaluation;8.Examining the mechanisms of action of the intervention strategies and moderators of their impact.

### Primary hypothesis

Among pregnant smokers (women reporting current smoking at antenatal booking) there will be a 5% increase in cotinine-confirmed 7-day point prevalence abstinence from a baseline prevalence of 16%, after introduction of MOHMQuit. This conservative estimate is based on the effectiveness of antenatal psychosocial smoking cessation interventions in the latest Cochrane review (RR 1.44, 95%CI 1.19-1.73) [17].

### Settings

The MOHMQuit trial will be implemented in nine public maternity services in NSW. The sites vary in size and are located in rural and urban contexts.

### Stepped-wedge cluster-randomised controlled trial design

The MOHMQuit trial uses a stepped-wedge cluster-randomised controlled trial design with random allocation of services to the intervention order [48–50]. All services begin as part of the control condition and are randomised to transition from the baseline condition (standard care) to the intervention at specific intervals or ‘steps’ [48, 49]. Each step will occur at two monthly intervals (Fig. 2). There is a 3-month intervention period during which the intervention is provided and embedded in the service, and a 5-month ‘washout period’ to allow time for women receiving care in the baseline period to complete their pregnancies, thus eliminating contamination between baseline and follow-up periods (Fig. 2). The trial was originally planned to run over 36 months at eight sites. However, due to the impacts of COVID-19 and some redesign work being completed in *e*Maternity, initiation of data collection and provision of the intervention was delayed. To compensate for the reduced time available for data collection, an additional site was added (site six in Fig. 2), and the timing of providing the intervention at the final site brought forward. This ensured the study was still adequately powered.

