**Intervention outcomes**				
Documented provision of smoking cessation support (SCS) at booking visit and any subsequent visits. Offer of: • referral to a smoking cessation service including NSW Quitline • behavioural support • nicotine replacement therapy (Aim 2)	Deidentified data extraction of specified variables for all births to eligible women at intervention sites	*e*Maternity^b^	Throughout the 32-month collection period	• *e*Maternity SCS scores will be calculated based on the documented provision of SCS in *e*Maternity for each woman at each visit. • Scores will be modelled using a linear mixed model. Fixed effects will be included for time, intervention, and the interaction of these. •Random effects for site and participant will be included to account for clustering by site, and repeated measures on participants. •The interaction term will directly compare the rate of change in SCS scores over antenatal visits between pre and post-intervention.
Self-reported: • Provision of Advice to quit smoking • Provision of Assistance to quit smoking • Provision of referral to a quit smoking service (e.g. NSW Quitline or local service). (Aim 3)	Study specific questionnaire	Clinicians	Before training and 6 months post-training	• The outcome measure will be a composite score of self-reported provision of SCS, calculated from the questionnaires completed by clinicians prior to training and at 6 months post-training. • Post-intervention clinician SCS scores will be modelled using a linear mixed model. Fixed effects will be included in the model for the pre-intervention SCS score and time. A random effect will be included for site to account for randomisation by cluster.
Women’s reported receipt of: • Advice on quitting • Referral to a quitting program • Written self-help materials (Aim 5)	Structured telephone interview^a^	Postpartum women	Within 2 weeks after giving birth	• Receipt of SCS reported by women will be modelled using logistic regression in a generalised linear mixed model framework. Fixed effects for time and intervention will be included in the model and a random effect for site will be used to account for randomisation by cluster.
**Mediators** (for more detail on the identified barrier, intervention types, behaviour change techniques and measures, see Additional file 1)				

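### The Aim 2 model has no calendar-time or record-version term, although its only data source was redesigned around the start; if the smoking cessation support (SCS) fields changed then, only baseline women would straddle two versions

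*Protocol article*

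**What the plan says.** The section on the stepped-wedge design gives two causes for the late start, COVID-19 and eMaternity: "some redesign work being completed in *e*Maternity, initiation of data collection and provision of the intervention was delayed". It gives no go-live date and no list of changed fields. It also sets the timetable: "Each step will occur at two monthly intervals", with a 3-month intervention period and a 5-month washout at each site.

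Table 2 (Intervention outcomes, Aim 2) names eMaternity as the only source and describes:

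- the population: "Deidentified data extraction of specified variables for all births to eligible women at intervention sites";
- the outcome: "Documented provision of smoking cessation support (SCS) at booking visit and any subsequent visits", scored for each woman at each visit;
- the window: "Throughout the 32-month collection period";
- the model: "Fixed effects will be included for time, intervention, and the interaction of these", with random effects for site and participant;
- the test: "The interaction term will directly compare the rate of change in SCS scores over antenatal visits between pre and post-intervention".

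The primary-outcome row of the same table differs: its time effect is there explicitly to adjust for secular trends.

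**The concern.** The Aim 2 population is defined by births, but its measurements are visits spread over the preceding months. Women who give birth early in the 32-month window had their booking and first visits before the window opened. If the record changed close to that moment, their early visits sit on one version and their later visits on another. Any such woman is in the baseline condition, because follow-up births come much later.

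A change in how SCS is captured would then appear as a step within the woman, over her visits, and the interaction tests change over visits. The listed terms would not absorb it. The wording of the test indicates that time in this model is visit time, so there is no separate calendar effect. A random participant intercept does not remove a within-woman step, and neither would a period effect defined by date of birth.

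If the older record captured less SCS, the baseline slope would be too steep, which hides a real gain in slope, while the pre/post difference in level would be exaggerated. If it captured more, both errors reverse.

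**Working it through.** **Plan's own figure.** Nine sites × 40 women × 12 periods = 4320, as in the Sample size section. The 12 periods are consistent with (32 − 3 − 5) / 2 = 12 two-month periods per site.

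**Inputs from the article.** Nine sites, 2-month steps, and an 8-month gap (3 + 5) between the end of baseline and the start of follow-up at each site.

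**Assumptions, not in the article.**

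- First site's baseline b = 4 months (range 2–8; Fig. 2 is not available).
- Booking-to-birth interval g = 6 months (range 5–8).
- Go-live L months before data collection (range 0–8).
- Births spread evenly over time.
- Visits before month 0 are scored.
- Births in the 8-month gap count in neither condition.

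**Share of baseline women with a visit on the older record.** Site k has baseline B(k) = b + 2(k − 1) months. With b = 4 this is 4, 6, …, 20, which sums to 108 site-months. The share is the sum of min(B(k), max(0, g − L)) divided by 108.

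| Go-live before start (L) | g = 6 | g = 6.5 |
|---|---|---|
| 0 months | (4 + 8 × 6)/108 = 52/108 = 48% | (4 + 6 + 7 × 6.5)/108 = 55.5/108 = 51% |
| 2 months | 9 × 4/108 = 33% | (4 + 8 × 4.5)/108 = 37% |
| 4 months | 9 × 2/108 = 17% | 9 × 2.5/108 = 21% |
| 6 months | 0% | 9 × 0.5/108 = 4% |
| 7 months or more | 0% | 0% |

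With L = 0, varying b from 2 to 8 and g from 5 to 8 gives 32% to 68%. That range includes a variant with the final site 2 months earlier, since the article says its timing was brought forward without saying by how much.

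**Follow-up women.** The earliest follow-up birth is at month b + 8. With b = 2 this is month 10. Even with g = 8 the booking visit is at month 2, after go-live. The share is 0% in every scenario.

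**Effect on the slope.** Take 8 equally spaced visits (assumed), with b = 4, g = 6 and L = 0. The share of baseline women on the older record at visits 1 to 8 is 0.481, 0.418, 0.354, 0.286, 0.214, 0.143, 0.071 and 0. The least-squares slope of these shares is −2.90 / 42 = −0.069 per visit. So each 1-point deficit in the older record adds about 0.069 points per visit to the baseline slope, or 7 × 0.069 = 0.48 points from first to last visit, and adds nothing to the follow-up slope. With b from 2 to 6 and g from 5 to 7 the figure is 0.051 to 0.086 per visit. It falls to 0.036 at L = 3 and to 0 at L = 6 (b = 4, g = 6).

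**Effect on the level.** The mean of the eight shares is 0.246, so the same deficit lowers the average baseline score by about 0.25 points.

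**The case against.** The strongest reply is that three things must all hold and the article states none of them: the redesign changed the SCS fields, it went live within one booking-to-birth interval of the start, and visits before the start are scored. If either of the first two fails, the artefact is zero. Holding back data collection while the record was redesigned may even show the team managing this risk. The scale of the SCS score is not given, so a shift per 1-point change cannot be called large or small. A go-live date and a covariate list could also sit in the analysis plan.

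Most of this stands. A reader might infer that the Aim 2 contrast is biased, or that half of the baseline is on an old form. The article does not support that. The figure of about one half needs go-live to coincide with month 0, and the range reaches zero once that date varies. Nor can the delay be put down to eMaternity alone, because COVID-19 is named too. The article lists better SCS recording in eMaternity among the intervention's systems elements, but does not link this to the redesign.

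Two things remain. First, the Aim 2 model is written out rather than deferred, and its listed terms would not absorb a recording change over calendar time. Second, if pre-start visits are not scored, the record artefact goes, but early baseline women then lack booking and early visits that follow-up women have. The two slopes would rest on different parts of pregnancy, so a rule is needed on either reading.

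**Conclusion.** The point holds in conditional form. As stated, the Aim 2 model has no protection against a change in its only data source around the start of the trial, and any women affected would all be in the baseline condition. The exposed share lies between 0% and about half of baseline women on the central layout, depending mainly on a go-live date that the article does not give. The sign of any bias is open, and its size depends on a recording change that may not have occurred.

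The result rests on the assumed first crossover, booking interval and visit spacing, on go-live at or before the start, and on the washout applying to Aim 2. Aim 2 is an intervention outcome. The primary outcome uses interview and cotinine data and is unaffected. Severity is low to moderate.

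**What to change.** Add to the Aim 2 model a visit-level fixed effect for record version (visit date before or after go-live) or for calendar period of the visit date. It must be defined by visit date, not birth date. State the go-live date, whether the SCS fields changed, and whether visits before the start of data collection are scored.

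The cost is one model term, one date from the eMaternity team and a small loss of precision. A single version term assumes the same shift at every visit, which can be checked once the changed fields are known.

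Restricting Aim 2 to women booked after go-live should be a sensitivity analysis only. With go-live at month 0, b = 4 and g = 6, it would drop 48% of baseline women and leave the first two sites, with 4 and 6 months of baseline, with no baseline at all. If the SCS fields did not change, or changed at least 7 months before the start, a sentence saying so is enough to settle the record-version point.
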